## Abstract

**Background:**

Approximately two-thirds of stroke survivors experience chronic upper limb paresis, and of them, 50% experience severe paresis. Treatment options for severely impaired survivors are often limited. Rehabilitation involves intensively engaging the paretic upper limb, and disincentivizing use of the non-paretic upper limb, with the goal to increase excitability of the ipsilesional primary motor cortex (iM1) and suppress excitability of the undamaged (contralesional) motor cortices, presumed to have an inhibitory effect on iM1. Accordingly, brain stimulation approaches, such as repetitive transcranial magnetic stimulation (rTMS), are also given to excite iM1 and/or suppress contralesional motor cortices. But such approaches aimed at ultimately increasing iM1 excitability yield limited functional benefit in severely impaired survivors who lack sufficient ipsilesional substrate.

**Aim:**

Here, we test the premise that combining Contralaterally Controlled Functional Electrical Stimulation (CCFES), a rehabilitation technique that engages the non-paretic upper limb in delivery of neuromuscular electrical stimulation to the paretic upper limb, and a new rTMS approach that excites intact, contralesional higher motor cortices (cHMC), may have more favorable effect on paretic upper limb function in severely impaired survivors based on recruitment of spared, transcallosal and (alternate) ipsilateral substrate.

**Methods:**

In a prospective, double-blind, placebo-controlled RCT, 72 chronic stroke survivors with severe distal hand impairment receive CCFES plus cHMC rTMS, iM1 rTMS, or sham rTMS, 2X/wk for 12wks. Measures of upper limb motor impairment (Upper Extremity Fugl Meyer, UEFM), functional ability (Wolf Motor-Function Test, WMFT) and perceived disability are collected at 0, 6, 12 (end-of-treatment), 24, and 36 wks (follow-up). TMS is performed at 0, 12 (end-of-treatment), and 36 wks (follow-up) to evaluate inter-hemispheric and ipsilateral mechanisms. Influence of baseline severity is also characterized with imaging.

**Conclusions:**

Targeting of spared neural substrates and rehabilitation which engages the unimpaired limb in movement of the impaired limb may serve as a suitable combinatorial treatment option for severely impaired stroke survivors.

**ClinicalTrials No:**

NCT03870672.

## 1. Introduction

Approximately, 37–50% of stroke survivors live with chronic severe upper limb paresis which is characterized by limited active range of motion, strength, and coordination from the shoulder to the hand/fingers and severely diminished ability to perform activities of daily living (1). Many rehabilitation therapies, such as constraint-induced movement therapy (CIMT) or intensive task-oriented training, are not feasible for this sub-population due to the requirement of residual movement in wrist, thumb, and fingers. Therefore, developing rehabilitation interventions that are both effective and applicable for stroke survivors with severe upper limb motor impairment is a major unmet clinical need.

Contralaterally controlled functional electrical stimulation (CCFES) is a therapy that can be used in stroke survivors with little to no residual hand/finger extension (2). CCFES delivers neuromuscular electrical stimulation to finger and thumb extensors to open the paretic hand with a stimulation intensity that is proportional to the degree of volitional opening of the non-paretic hand wearing an instrumented glove. Therefore, as patients open their non-paretic hand, the paretic hand opens as well to allow participation in task-oriented practice. In a recent RCT including chronic stroke survivors with moderate and severe upper limb impairment (*N* = 80), CCFES led to greater improvements in dexterity compared to cyclic neuromuscular electrical stimulation (cNMES) at 6-months post-treatment. Though significant between-group differences in upper limb motor impairment (Upper Extremity Fugl-Meyer; UEFM) were not seen, unpublished secondary analyses reveal UEFM gains were in favor of the CCFES group in severely impaired participants (*N* = 28). Participants with severe impairment at baseline experienced greater UEFM gains at 6-weeks after CCFES, 2.8 (95% CI, 0.8 to 4.8) than after cNMES, 0.8 (95% CI, −0.3 to 1.9), *p* = 0.09. UEFM gains were even larger in patients with severe impairment who were < 2years post-stroke, 4.5 (95% CI, 2.4 to 6.6) after CCFES vs. 0.8 (95% CI, −0.6 to 2.3) after cNMES, *p* = 0.006. Based on minimal clinically important difference (MCID) of 4.25 for UEFM (3), 50% of severely impaired patients < 2years post-stroke, who had received CCFES, attained clinically meaningful UEFM gains, compared to 9% of participants, who had received cNMES, *p* = 0.06. But since this advantage seen on UEFM after CCFES did not translate to improvement in functional abilities (Arm Motor Ability Test) across severely impaired stroke survivors, an opportunity exists to build upon the gains achieved by augmenting CCFES with another technique that may enhance the neuroplastic effects of CCFES.

Noninvasive repetitive transcranial magnetic stimulation (rTMS) can enhance functional gains associated with rehabilitation. Cortical areas involved in plastic mechanisms are targeted to potentiate their contribution toward recovery (4, 5). High-frequency rTMS (≥5*Hz*) can increase cortical excitability, while low-frequency rTMS (≤ 1*Hz*) can suppress cortical excitability. In stroke, ipsilesional primary motor cortex (iM1) is the most common target. Typically, high-frequency rTMS is delivered to increase excitability of iM1 directly, or low-frequency rTMS is given to suppress the inhibitory influence of contralesional motor areas and thereby increase excitability of iM1 indirectly. Regardless, severe damage to ipsilesional corticospinal pathways limit gains in function that can be made with iM1 facilitation (6, 7).

Our group and subsequently other groups have tested a new approach to promote motor function in survivors with more severe motor impairment and injury. This approach involves facilitating the excitability of contralesional higher-motor cortices (cHMC) with high-frequency rTMS, based on the view that these regions can make positive contributions to ipsilateral (paretic) upper limb movement *via* extensive bi-hemispheric connections and alternate, uncrossed pathways in the absence of sufficient ipsilesional substrate (8–10). Transient disruption of cHMC activity produces greater impairment in movement of the paretic limb in stroke survivors with more severe motor impairment (10–12). Transient disruption of iM1 activity does not have such an effect, indicating cHMC may be crucial for behavioral restitution in survivors with severe motor impairment and injury. Likewise, we have found that facilitation of cHMC activity with high-frequency rTMS produces greater improvement in motor control than facilitation of iM1 in survivors with more severe motor impairment, reinforcing the value of these intact targets in recovery (11, 13).

Therefore, we hypothesized that CCFES when combined with facilitation of cHMC *via* high-frequency rTMS would produce synergistic gains in motor function in survivors with more severe motor impairment. CHMC would be a favorable target not just based on its potential to make positive contributions to paretic limb movement in the absence of sufficient ipsilesional substrate but also because of its specialized role in bilateral control, which underlie CCFES-mediated training (8, 10).

In an ongoing randomized controlled trial of stroke survivors with severe chronic hand motor impairment, we are testing whether CCFES combined with rTMS facilitation of cHMC produces a greater reduction in motor impairment and perceived disability, and larger gains in functional ability as compared to CCFES combined with rTMS facilitation of iM1 and CCFES combined with sham rTMS (**Hyp 1**). CCFES with rTMS facilitation of cHMC will produce greater motor functional gains achieved with increases in the excitability of uncrossed pathways and bi-hemispheric connections (**Hyp 2**). We anticipate the severity of baseline impairment and extent of corticospinal damage will mediate the overall treatment effects (**Hyp 3**).

## 2. Methods

### 2.1. Participants

This study is a randomized, sham-controlled, and double-blinded clinical trial of up to 72 participants who had suffered a stroke at least 6 months previously and who continue to experience severe chronic upper limb motor impairment. Clinical assessment of the motor impairment is performed by an occupational therapist. “Severe” motor deficit is being defined as the inability to extend wrist ≥10-degrees, extend/abduct thumb ≥10-degrees, or extend two other digits ≥10-degrees (exclusion criteria in CIMT studies). This clinical motor criterion was chosen because it has a better prospect of being generalizable and was also used to define “severe” motor impairment in the previous CCFES clinical trial (2). Participants are required to have functional paretic hand opening in response to neuromuscular electrical stimulation of finger or thumb extensors to ensure it is feasible for them to undergo CCFES-mediated rehabilitation (See Inclusion Criteria, Table 1). Participants are excluded for contraindications to TMS and magnetic resonance imaging (MRI), including cardiac pacemaker, history of seizures, substance abuse, metallic implant in the head etc. determined by a stroke neurologist (See Exclusion Criteria, Table 2). Participants are being recruited from the Cleveland Clinic, Cleveland, OH. The trial is governed by human research protection policies of the Cleveland Clinic Institutional Review Board. All participants provide written informed consent before participating.

**Table 1 T1:** Inclusion criteria.

• Age 18–90 years old at the time of randomization
• >6 months since a first clinical cortical or subcortical, ischemic or hemorrhagic stroke
• Severe upper limb hemiparesis defined as lacking ≥10-degrees active wrist extension or ≥10-degrees active thumb abduction/extension or ≥10-degrees active extension in at least two additional digits (i.e., will not meet minimum constraint induced movement therapy criteria)
• Memory of at least 2 out of 3 items after 30 min
• Able to perform 3-stage command
• Full volitional hand opening/closing of the non-paretic hand
• Ability to follow instructions for putting on and operating the contralaterally controlled functional electrical stimulation (CCFES) device or have a caregiver available to provide assistance
• Adequate active movement of shoulder and elbow to position the paretic hand on one's lap for performance of functional task practice and CCFES-assisted hand opening exercises
• Skin intact on hemiparetic arm
• Surface electrical stimulation of the paretic finger and thumb extensors produces functional hand opening without pain (this will exclude patients who have too much flexor spasticity)
• Able to hear and respond to cues from stimulator
• Completed occupational therapy at least 2 months prior to enrollment (no concomitant OT)

**Table 2 T2:** Exclusion criteria.

• Concomitant neurologic diagnosis of peripheral nerve injury, Parkinson's disease, spinal cord injury, traumatic brain injury, or multiple sclerosis
• Brainstem stroke
• Severe shoulder or hand pain, i.e., unable to position hand in the workspace without pain
• Insensate to touch on forearm or hand
• Uncompensated hemi-neglect (extinguishing to double simultaneous stimulation)
• Cardiac pacemaker or other implanted electronic system
• History of potentially fatal cardiac arrhythmia
• Diagnosis (apart from stroke) that substantially affects paretic arm and hand function
• Deficits in communication that interfere with reasonable study participation
• Lacking sufficient visual acuity to see the stimulator's display
• Concurrent enrollment in another investigational study
• Pregnancy
• Metal implants in the head
• Seizure as an adult or diagnosed with epilepsy
• Current abuse of alcohol or illicit drugs
• Botulinum toxin injections to any upper extremity muscles within 2 months of enrolling
• Taking any anti-convulsant
• Taking bupropion/valbutrin (other antidepressants are acceptable)
• History of fainting spells of unknown/undetermined etiology
• Implanted pumps, deep brain stimulator, shunts, nerve stimulators
• Current diagnosis of carpal tunnel syndrome
• Previous adverse reaction to transcranial magnetic stimulation

### 2.2. Randomization

Participants are assigned to one of three treatment groups—CCFES plus 5 Hz rTMS of cHMC, CCFES plus 5 Hz rTMS of iM1, or CCFES plus sham rTMS of cHMC/iM1 using an adaptive randomization algorithm (14, 15). The algorithm is designed to minimize group imbalances on 4 key participant characteristics: (1) time post-stroke (<2 years vs. ≥2 years), (2) presence of cortical vs. subcortical lesion, (3) presence of active wrist extension vs. none and (4) paresis of dominant vs. non-dominant side. Two years post-stroke was chosen as stratification cutoff because our previous CCFES trial had reported a higher likelihood of response in participants within that time-frame (2). With the inclusion of the wrist extension, we expect that baseline differences in degree of distal upper limb severity will be minimized. Balancing across the three groups can still be challenging. Allocation is concealed by storing group assignments in a binder to which only the study coordinator and rTMS interventionists have access.

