### 2.3. Blinding

The assessors, the therapist, and the participants are all blinded to group assignment. Though participants are aware of which hemisphere the rTMS is being applied, they are not aware of whether real or sham rTMS is being delivered. Stimulation parameters (intensity, frequency and the total number of pulses), stimulation site (iM1 or cHMC) and type of stimulation (real or sham) are verified by rTMS interventionists before rTMS is delivered. Integrity of blinding is determined at the end of the intervention period using a questionnaire which requires participants and assessors to guess the group allocation.

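### The binder in section 2.2 protects blinding after assignment but does not establish that the next allocation is concealed

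*Protocol article*

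**What the plan says.** Section 2.2 of the protocol article gives both the allocation method and the means of concealing it.

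- **Method.** "Participants are assigned to one of three treatment groups", "using an adaptive randomization algorithm" that is specified by citation. "The algorithm is designed to minimize group imbalances on 4 key participant characteristics": time since stroke, cortical or subcortical lesion, active wrist extension present or not, and paresis of the dominant or non-dominant side. All four are two-level baseline factors.
- **Concealment.** "Allocation is concealed by storing group assignments in a binder to which only the study coordinator and rTMS interventionists have access".

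Section 2.3 (Blinding) adds: "The assessors, the therapist, and the participants are all blinded to group assignment". The coordinator and the rTMS interventionists are not in that list. The interventionists must know the arm of each participant they treat, since stimulation site and "type of stimulation (real or sham) are verified by rTMS interventionists before rTMS is delivered".

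Section 2.1 (Participants) names two eligibility roles. For the motor criterion, "Clinical assessment of the motor impairment is performed by an occupational therapist". Contraindications to TMS and MRI are "determined by a stroke neurologist". Neither role is listed as having access to the binder. Recruitment is at one centre.

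**The concern.** Allocation concealment means that nobody who can affect whether, when or how a participant is entered knows or can predict the next assignment. Blinding limits knowledge of assignments after they are made. The binder sentence describes the second and calls it the first.

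The distinction matters more here than with a fixed sequence. Under a minimising algorithm there is no stored next assignment to lock away. The favoured arm is computed from the assignments so far and the new participant's factor values. A record of past assignments is therefore part of what is needed to predict the next one, and the mechanism offered as concealment is that record, open to two roles. If the binder instead held assignments prepared in advance, which would not fit the algorithm described, concealment from those two roles would be weaker still.

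What is at stake is selection bias. A person who could foresee the arm and also influence entry could time a borderline candidate or settle an ambiguous factor value accordingly. Blinded outcome assessment acts too late to prevent that, and the linear mixed model in section 7 cannot adjust for selection on unmeasured characteristics.

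**Working it through.** The article gives no figure for predictability, so there is none to reproduce. The check asks how far someone with sight of past assignments beats chance.

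**Inputs from the article:** 72 participants (section 6), three arms and four two-level factors (section 2.2). Equal allocation is inferred from 22 per group in section 6. A blind guess is then right 1/3 = 33% of the time, or 24 of 72.

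**Assumptions, because the article does not give them:** 50% prevalence for each factor; marginal minimisation with the imbalance score summed over the four factors; the arm with the lowest score is assigned with probability p, with ties broken at random. The value p = 1 is a deterministic rule, and lower values add a random element.

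**Observer A** sees past assignments only and guesses the arm with the fewest participants. **Observer B** also knows every participant's factor values and the scoring rule, and guesses the arm the algorithm favours.

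| p | A: assignments only | B: full information | Chance |
|---|---|---|---|
| 1.0 | 58% | 89% | 33% |
| 0.8 | 52% | 73% | 33% |
| 0.7 | 49% | 65% | 33% |
| 0.5 | 42% | 48% | 33% |

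**Arithmetic check for B.** Let u be the share of participants for whom one arm is uniquely favoured.

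- At p = 1, u is about 0.79. The remaining 0.21 are ties, guessed correctly 1/2 of the time (two-way) or 1/3 (three-way). The total lies between 0.79 + 0.21 × 1/3 = 0.86 and 0.79 + 0.21 × 1/2 = 0.895. The simulated 0.89 fits.
- At p = 0.8, u is about 0.81. A two-way tie is guessed with probability 0.5 × 0.8 + 0.5 × 0.1 = 0.45. The total is 0.81 × 0.8 + 0.19 × 0.45 = 0.73, as simulated.

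**Sensitivity.** Using a variance score in place of a range score, or handling ties differently, moves the results by up to about three percentage points (for B, 86% at p = 1 and 45% at p = 0.5). For B, unequal factor prevalences of 40, 50, 30 and 50% give nearly the same results: 89%, 72% and 63% at p = 1.0, 0.8 and 0.7.

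**In participants.** A is right for about 0.42 × 72 = 30 to 0.58 × 72 = 42 of 72. B is right for about 0.48 × 72 = 35 to 0.89 × 72 = 64. Chance gives 24.

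**The case against.** A reader might infer that past assignments largely give away the next arm and that allocation in this trial is not concealed. The article does not support either statement, for these reasons.

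- **The random element is not stated.** The method is called adaptive randomization and is specified by citation. With a strong random element the gain over chance is modest (42% or 48% against 33% at p = 0.5). Leaving that detail out of an article is not itself a fault.
- **The binder is said to hold assignments, not factor values.** The figures up to 89% need the factor values of all earlier participants and the scoring rule. A coordinator may have these from other records, but that is a further assumption. From the binder alone the range is 42-58%.
- **No one with binder access is said to control entry.** The two eligibility roles named in section 2.1 are an occupational therapist and a stroke neurologist, and neither is given access. Prediction by someone with no influence over entry does no harm.
- **The route through miscoding is thin.** Section 4.4 allows lesion categories to be combined, but it describes an imaging measure and not the coding rule for the randomization factor. Time since stroke and side of paresis leave little discretion.
- **Interventionists will learn arms in any case.** At a single centre they could rebuild part of the history without a binder.

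All five stand as limits on the conclusion. They do not rescue the sentence itself. The article did not leave concealment to a fuller document: it states a mechanism, and that mechanism does not serve the stated purpose. Every setting examined puts prediction above chance.

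**Conclusion.** The point holds in a limited form. The binder restricts knowledge of assignments already made and so supports blinding. It does not establish concealment of the next allocation, because under a minimising algorithm the two roles with access can predict the next arm better than chance. How much better depends on the unstated random element and on what else they know. The figures rest on the assumed scoring rule and factor prevalences.

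Whether this leads to selection bias depends on one further assumption: that someone with access influences enrolment, its timing or the coding of the four factors. The article neither says this nor rules it out. It is a weakness in a stated safeguard, not evidence that the comparison is biased. It is worth correcting because the remedy is cheap, and selection bias could not be removed at analysis.

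**What to change.** Replace the binder sentence in section 2.2 with a short paragraph providing that:

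1. each assignment is generated only after consent, eligibility, baseline UEFM and the four factor values have been recorded and locked;
2. it is generated by an existing team member with no part in screening or enrolment, for example the statistician who maintains the algorithm, and released only to the rTMS interventionist treating that participant;
3. anyone who screens, enrols or codes the factors, including the coordinator if so involved, has no access to cumulative assignments;
4. rTMS interventionists take no part in eligibility decisions or factor coding. This separation matters most for them, since they must know the arms of those they treat.

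If this is already the practice, only the text needs correcting.

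**Cost:** one procedural paragraph and a change of access rights, with no additional staff, visits or participants. The drawback is that the coordinator can no longer look up an arm, and unblinding requests go through the holder of the allocations.

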### 2.3. Blinding

The assessors, the therapist, and the participants are all blinded to group assignment. Though participants are aware of which hemisphere the rTMS is being applied, they are not aware of whether real or sham rTMS is being delivered. Stimulation parameters (intensity, frequency and the total number of pulses), stimulation site (iM1 or cHMC) and type of stimulation (real or sham) are verified by rTMS interventionists before rTMS is delivered. Integrity of blinding is determined at the end of the intervention period using a questionnaire which requires participants and assessors to guess the group allocation.

## 3. Intervention

For all groups, treatment lasts 12 weeks and consists of 22 sessions of group-specific rTMS for 21 min followed immediately by 1 h of therapist-guided CCFES-mediated functional task practice performed in the laboratory (two sessions per week except on weeks 6 and 12, which include an assessment session). In addition to this, participants self-administer 10 sessions per week of CCFES-mediated repetitive hand opening exercises at home (no more than two sessions per day separated by at least 2 h).

